#### Secondary endpoints

We will compare the mean change in EQ-5D-5L index score and visual analogue score, EORTC QLQ-C30 and EORTC QLQ-BR45 scale scores in the intervention and control arm in simple and multiple linear regression models including potential covariates.

We will compare the mean change in the three HADS scale scores in the intervention and control arm in simple and multiple linear regression models including potential covariates. Based on the continuous overall psychological distress score, patients are classified as ‘distressed’ when they have a score of ≥ 8, and ‘not distressed’ when they have a score < 8. Frequency, percentages, and any appropriate 95% confidence intervals of this dichotomization at baseline and 3 months will be presented. Chi-square or Fisher’s exact test will be used to compare the level of distress between the intervention and control arms.

We will present the mean rate of resource utilization and cost per patient in the two groups by type of resource (primary, secondary and social care) and for total NHS resources used. Simple and multiple linear regression models including potential covariates will compare the mean rate of total resource utilization and the mean cost per patient in the two groups.

We will describe the average scale scores of the four validated measures in the two groups at the four time points and show graphically the trend in scale scores in each group. We will also compare the mean change in scale scores of the measures across the four time points between the intervention and control arm using a mixed models approach.

To describe OWise uptake, the average number of times logging in at daily intervals throughout the follow-up period will be described and the trend of mean logging in over time will be graphed. We will also show the average frequency of use for each function of the tool over time.

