##### Hospital Anxiety and Depression Scale (HADS)

This 14-item questionnaire measures psychological distress with seven items assessing anxiety, seven items assessing depression and the summed total score reflecting the level of psychological distress [37]. Three continuous scales will be calculated (anxiety, depression, and overall psychological distress) according to HADS guidelines [37, 38]. Higher scores indicate more psychological distress [37, 38]. The HADS has evidence of reliability and validity in early stage breast cancer patients [36, 39].

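### The distress analyses do not fix baseline HADS or the randomization strata as covariates, which costs power on a secondary outcome; the cut of 8 on the total needs only a clarification

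*Protocol article*

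**What the plan says.** The HADS section describes 14 items: "seven items assessing anxiety, seven items assessing depression and the summed total score reflecting the level of psychological distress". Three continuous scales are to be scored.

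Under Secondary endpoints, the continuous scales come first: "We will compare the mean change in the three HADS scale scores in the intervention and control arm in simple and multiple linear regression models", the multiple models including potential covariates. The dichotomy follows. "Based on the continuous overall psychological distress score", "patients are classified as ‘distressed’ when they have a score of ≥ 8". Proportions "of this dichotomization at baseline and 3 months will be presented", and a chi-square or Fisher's "exact test will be used to compare the level of distress between the intervention and control arms". Later in the section, a mixed model compares change in the four questionnaires over all four time points.

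The general Analysis section adds two rules. Multivariable models use logistic regression for binary outcomes and linear regression for continuous ones. A covariate enters if its univariate p value is below 0.1. No list of candidate covariates is given, and the baseline value of the outcome is not named as one.

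The Randomization section stratifies by age group (under 60, 60 and over) and center. The Study design section has both groups complete the questionnaires at baseline. The distress objective concerns a smaller rise in distress at 3 months, controlling for potential covariates.

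**The concern.** Baseline HADS should be one of the strongest predictors of HADS at 3 months, and it is collected in both arms. Age group and center are built into the randomization. A rule that admits covariates only on a univariate p value leaves the use of all three to the data. The simple regression on change and the two-by-two test leave them out altogether.

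Nothing is biased by this, because the arms are randomized. What is at stake is precision in a trial sized for about 47 completers per arm on a different outcome. There is also room for choice: change regression (simple or multiple), mixed model, chi-square test and logistic model could all be read as answering the distress objective, and none is named as leading.

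A smaller matter is the cut-off. It is applied to the sum of two seven-item scales, and the sentence that sets it gives neither a reason nor a citation. A score of 8 is an average of 8/14 = 0.57 per item on the total and 8/7 = 1.14 per item on one subscale, so the same number means something different on each.

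**Working it through.** **Sample size, to fix the number per arm.** From the Sample size section: difference 5.90, SD 10.0, two-sided alpha 0.05, power 80%. The normal formula gives n = 2 × (1.96 + 0.8416)² × 10² / 5.90² = 45.1, so 46. The t-distribution version gives 46.08, so 47, as stated. With 23% attrition, 47/0.77 = 61.04, stated as 61. These figures reproduce. They concern PAM-13; no figure is given for distress.

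**Assumptions.** The article gives no HADS SD, distress rate or baseline correlation. I assume a normal score with equal SD at both times, a true effect of 0.5 SD, 47 per arm, and a baseline correlation r of 0.3, 0.5 or 0.7. For the dichotomy I place the cut at the control median. The strata are left out of the calculation.

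**Continuous score.** In units of the 3-month variance, the change score has variance 2(1 − r) and the baseline-adjusted score 1 − r². Their ratio (adjusted to change) is (1 + r)/2 = 0.65, 0.75, 0.85. Power is approximately Φ(0.5 × √(47/2) / √variance − 1.96), where 0.5 × √23.5 = 2.424.

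| r | Variance, change | Variance, adjusted | Power, change: formula / simulated | Power, adjusted: formula / simulated |
|---|---|---|---|---|
| 0.3 | 1.40 | 0.91 | 53.5% / 51.9% | 71.9% / 70.9% |
| 0.5 | 1.00 | 0.75 | 67.9% / 67.5% | 79.9% / 78.7% |
| 0.7 | 0.60 | 0.51 | 87.9% / 87.3% | 92.4% / 92.1% |

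The simulations used 1,500 trials per setting and agree with the formula. In sample-size terms, the unadjusted change score needs 2/(1 + r) = 1.54, 1.33 or 1.18 times as many patients for the same precision.

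**Two-by-two test.** With 50% of controls above the cut, a 0.5 SD shift leaves Φ(−0.5) = 30.9% in the intervention arm. The two-proportion formula at 47 per arm gives 47% power.

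| r | Chi-square, simulated | Logistic with baseline, simulated |
|---|---|---|
| 0.3 | 46.9% | 49.5% |
| 0.5 | 46.1% | 52.5% |
| 0.7 | 44.9% | 61.1% |

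Adding baseline therefore gains about 3 to 16 percentage points, still well below the continuous analysis.

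**Would the p < 0.1 rule select baseline anyway?** Under these assumptions the correlation between change and baseline is −√((1 − r)/2) = −0.59, −0.50, −0.39. With 94 patients, t = correlation × √92 / √(1 − correlation²), about −7.0, −5.5 and −4.0, all with p near 0.0001 or smaller. So the multiple regression would almost always admit baseline HADS, provided it is on the candidate list. The article does not say that it is.

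**The case against.** The strongest reply is that most of the remedy is already in the plan. The sentence just before the cut-off compares continuous HADS change, with and without covariates. A mixed model uses all time points. The general rule supplies logistic regression for binary outcomes, and distress is the only binary outcome named, so the chi-square test reads as the unadjusted companion to that model. A reader might infer that distress is compared only by a two-by-two test, or that the plan disregards baseline. The article does not support either reading: a change score uses baseline, and the low power of the dichotomy does not carry over to the continuous analyses.

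It is also fair to say that if baseline HADS is a candidate covariate, the screening rule would nearly always select it. The multiple regression would then recover the gain. That stands, and it limits the practical loss. It does not remove the point: the candidates are not listed, age group and center might not pass the screen, the simple regression and chi-square test stay unadjusted, and no analysis is named as leading.

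On the cut-off, a reader might infer that 8 is a subscale threshold misapplied to the total. The article cannot show this. It gives no item range and no threshold for either score. It does cite scoring guidelines in the HADS section, and a condensed article may leave the rationale to the full protocol.

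Finally, covariate selection by p value affects every endpoint, not only HADS. That is correct; distress is where the loss can be shown most plainly.

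**Conclusion.** The point holds as a matter of efficiency and pre-specification, not validity. Under the assumed 0.5 SD effect and 47 per arm, fixed baseline adjustment raises power over the unadjusted change score by about 19, 11 and 5 percentage points at r = 0.3, 0.5 and 0.7. Over the chi-square test, logistic regression with baseline gains about 3, 6 and 16 points. The effect size, correlations, normality and placement of the cut are all assumptions, and the gain on the continuous score shrinks as the correlation rises. Any further gain from the strata was not quantified.

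The cut-off is a request for confirmation only. The effect is confined to one secondary outcome. The primary outcome and the sample size are untouched. Severity is low.

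**What to change.** 1. For the distress objective, name as the lead analysis a linear regression of the 3-month HADS total on arm, with baseline HADS total, age group and center as fixed covariates that are not subject to the p < 0.1 screen. State that the other HADS analyses are supporting.
2. Keep the distressed/not distressed split descriptive. If the arms are to be compared on it, replace the chi-square or Fisher test with logistic regression that has baseline HADS total as a fixed covariate.
3. Confirm against the scoring guidelines already cited that the cut of 8 is meant for the 14-item total and not for a seven-item subscale, and add the reference at that sentence.

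The cost is a few lines of analysis text and one guideline check. No new data are needed. The article reports recruitment as pending and questionnaire data as inaccessible to researchers until extraction at study end, so the change can be made before outcomes are seen.

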#### Sensitivity analysis

Per-protocol analysis will be performed as a sensitivity analysis to assess the impact of contamination on the primary analysis. In the sensitivity analysis, all participants in the control arm that report using OWise will be excluded. If the sensitivity analysis produces results dissimilar from the primary analysis, we will determine that the primary results are not robust and further research is required.

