**Methods:**

This randomized controlled trial with early stage breast cancer patients will assess the effect of OWise use on patient activation at 3 months from diagnosis measured by the PAM-13 questionnaire. We will also assess differences in changes in health-related quality of life, psychological distress, health status, and National Health Service (NHS) health resource utilization over the first year from diagnosis. Participants will be randomly allocated (1:1) to standard care or standard care plus OWise. Participants will complete questionnaires before starting anti-cancer treatment and at 3, 6, and 12 months from diagnosis. Clinical and patient-reported outcome data will be linked to health resource utilization data from Discover, an integrated care record of primary, secondary, and social care in North West London. We will measure contamination in the control group and adjust the sample size to mitigate the dilution of effect estimates. A per-protocol analysis will be conducted as a sensitivity analysis to assess robustness of the primary results.

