#### Contamination

Patient responses to items at each measurement time point will indicate contamination. A set of 19 items will ask participants to identify the use of supportive care services including self-management mobile phone applications or websites. If a participant says yes, we will ask them to name the source in a free-text box to determine whether or not OWise has been used. Prior to recruitment close, the statistician will assess the level of contamination and increase the sample size commensurately [43].

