#### Patient-reported outcome measure data

Participants will complete PROMS using PROFILES (Patient-Reported Outcomes Following Initial treatment and Long-term Evaluation of Survivorship), an online PROM collection and data management system developed in the Netherlands and implemented at the Royal Marsden [44]. Follow-up time points will be managed by the Royal Marsden as the coordinating center. PROM responses cannot be viewed by the researcher or clinical team until extracted at the end of the study when it will be linked to other study data by the study identification number.

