### Sample size

Sample size calculations are based on the change in PAM-13 score from baseline to 3 months. A difference of four points is considered clinically relevant [29, 45]. In a similar study, the mean PAM-13 score at baseline for the intervention group was 61.3 (SD 16.61) and 67.9 (SD 16.85) at 3 months [46]. For the control group, the study reported a mean PAM-13 score at baseline of 62.1 (SD 17.30) and 62.8 (SD 14.94) at 3 months. Based on these findings, this study is planned to detect a mean change difference of 5.90 assuming a common standard deviation of 10.0. Using an 80% power, the study will recruit 47 patients per group. This was calculated using a two-sided test with alpha = 0.05. We will increase the sample size taking 23% attrition at 3 months into account (47/(1–0.23)) to 61 patients per group [47] and, as mentioned above, increase the sample size accordingly if contamination is found near the end of recruitment.

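### The contamination sensitivity analysis excludes only control users of OWise and reads any dissimilar result as non-robustness, although a gap is expected if OWise works and contamination occurs

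*Protocol article*

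**What the plan says.** The Sensitivity analysis section of the protocol article defines the per-protocol analysis by one exclusion: "all participants in the control arm that report using OWise will be excluded". It then fixes the reading: "If the sensitivity analysis produces results dissimilar from the primary analysis, we will determine that the primary results are not robust", and further research is called for. It states no size, direction or time limit. The Discussion repeats that this analysis tests the robustness of the ITT result.

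Around it, the protocol says:
- Control group: participants are not told about OWise but may use it.
- Intervention group: use is voluntary. OWise uptake is recorded by timestamps, and the per-protocol definition leaves non-users in.
- Contamination: use is asked at every questionnaire, so up to 12 months. Also, "Prior to recruitment close, the statistician will assess the level of contamination and increase the sample size commensurately".
- Abstract: the trial will "adjust the sample size to mitigate the dilution of effect estimates".
- Patient-reported outcome measure data: "PROM responses cannot be viewed by the researcher or clinical team until extracted at the end of the study".

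**The concern.** The two analyses respond differently to contamination. ITT keeps control users, so a working tool shows a smaller difference. The exclusion analysis removes them, so that loss disappears. The rule treats the resulting disagreement as evidence against the primary result, when a larger estimate after exclusion is what dilution of a real benefit would produce. Without contamination nobody is excluded, the analyses coincide and the rule cannot operate.

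The exclusion is also made after randomisation and in one arm only. Controls who find OWise unaided select themselves, while the comparable people in the intervention arm stay in. Any difference in how such people would have changed without the tool enters the estimate as bias. With no time limit, a control participant who first used OWise after month 3 would be dropped from the 3-month comparison because of something that followed the endpoint.

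The Discussion presents contamination as the central design challenge. At stake is whether a sound result is reported as unreliable.

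**Working it through.** **Inputs from the Sample size section.** The planning effect: "this study is planned to detect a mean change difference of 5.90 assuming a common standard deviation of 10.0". The other inputs are 47 evaluable per arm, power of 80%, a two-sided 5% level and 23% attrition.

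**The plan's own figure.** n = 2 × (10 × (1.960 + 0.842) / 5.9)² = 45.1, so 46 per arm by the normal approximation. The t-test version gives 46.08, so 47. Then 47 / 0.77 = 61.04, stated as 61, and 2 × 61 = 122. The figures reproduce; the sample size is not at fault.

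**Assumptions.** The protocol gives no contamination rate, so c runs from 5% to 30%. Let delta be the untreated change of people who would seek the app minus that of people who would not, taken as 0, +5 or −5. The effect D = 5.9 is constant and intervention uptake is full unless stated.

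**Formulas.**
- Expected ITT = D(1 − c)
- Expected exclusion estimate = D + c × delta
- Expected gap = c(D + delta)

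With uptake u below 1, the first two become D(u − c) and D × u + c × delta. The gap is unchanged, so it does not depend on full uptake.

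| c | ITT | Exclusion, delta 0 | Gap, delta 0 | Exclusion, delta +5 | Exclusion, delta −5 |
|---|---|---|---|---|---|
| 5% | 5.61 | 5.90 | 0.30 | 6.15 | 5.65 |
| 10% | 5.31 | 5.90 | 0.59 | 6.40 | 5.40 |
| 20% | 4.72 | 5.90 | 1.18 | 6.90 | 4.90 |
| 30% | 4.13 | 5.90 | 1.77 | 7.40 | 4.40 |

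At c = 20% the gap is 0.2 × (5.9 + 5) = 2.18 for delta +5, and 0.2 × (5.9 − 5) = 0.18 for delta −5. It vanishes only if delta offsets D.

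**How often the analyses disagree.** In simulation (47 per arm, SD 10, two-sided t tests, 8,000 trials per setting, D = 5.9), they differ on significance in 4.8%, 9.0%, 16.5% and 23.4% of trials at the four values of c with delta = 0. With delta = +5 the figures are 7.8%, 15.5%, 30.3% and 42.8%.

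**No true effect, delta = +5.** The expected exclusion estimate is c × 5: 1.0 point at c = 20% and 1.5 at 30%. The simulated rejection rate, nominally 5%, is about 7 to 8% at c = 20% and about 10% at 30%. At c = 10% it is under 6%.

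**What a larger sample does.** At c = 20%, 80% power needs 2 × (10 × 2.802 / 4.72)² = 70.5, so 71 per arm by the normal approximation. Expected ITT stays at 4.72. Power is restored; dilution is not.

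**An alternative that keeps everyone as randomised.** The complier-average estimate is ITT / (u − c). At u = 1 and c = 20% it is 4.72 / 0.8 = 5.9, whatever delta is. Its precision follows from the ITT standard error, 10 × √(2/47) = 2.06:
- u = 100%: 2.06 / 0.8 = 2.6.
- u = 60% of the whole arm: 2.06 / 0.4 = 5.2.
- 60% uptake only among those who would not seek the app, so 0.2 + 0.8 × 0.6 = 68% overall: about 4.7 in simulation.

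**The case against.** Much can be said for the plan. ITT stays primary, and the rule replaces neither its estimate nor its p value. The text says dissimilar, and a threshold could sit in an analysis plan that is not shown. Contamination may be slight: the tool is not named at invitation, controls are not told of it, and the Discussion calls UK use low. At 5% use with delta = 0 the expected gap is 0.3 points. The complier-average estimate answers a different question, the effect of use rather than of offering the tool. It needs allocation to act only through use, measures use differently in the two arms and loses precision.

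These points limit the size of the problem. They do not repair a rule without direction: a threshold alone would still count a larger estimate after exclusion against ITT.

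Three stronger readings are not supported:
- **That the exclusion manufactures benefit.** The endpoint is change in PAM-13, so a higher starting level is largely differenced out, and high starters on a scale capped at 100 might change less. Delta may be negative; at −5 and c = 20% the estimate is 4.9, below the true 5.9. With delta = 0 and full uptake the exclusion recovers 5.9.
- **That the rule overturns a positive trial.** It labels the result not robust and calls for more research, no more.
- **That the early look at contamination is impossible because responses are locked.** The bar names the researcher and clinical team, whereas the look belongs to the statistician, whom the Dissemination section lists separately as having data access. Only the timing of extraction is in tension.

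**Conclusion.** The concern holds for the verdict rule and, conditionally, for the exclusion. If OWise works and some controls use it, a gap of c(D + delta) is expected, and the rule can call a valid, conservative ITT result not robust. This needs no assumption that control users are unusual: at D = 5.9 and delta = 0 the gap runs from 0.3 points (5% use) to 1.8 (30% use). It fails only if delta cancels D.

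Separately, the exclusion estimate carries a bias of c × delta of unknown sign: 1 point either way at 20% use and delta of ±5, against the 4 points named in the Primary objective. The values of c and delta are assumptions, as is uptake wherever it enters; if use is as low as the protocol suggests, the practical effect is small.

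Two minor wording points remain. The abstract credits the sample-size increase with mitigating dilution of the estimate, when it protects power. The Contamination and Patient-reported outcome measure data sections leave unclear when the contamination items are extracted.

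**What to change.** 1. Delete the rule that a dissimilar result makes the primary result not robust. Keep ITT as the answer, and state in advance that a larger effect after allowing for contamination is consistent with dilution and does not count against ITT.
2. Replace the exclusion with a complier-average estimate as a supportive analysis: allocation as instrument, OWise use by 3 months as exposure in both arms. Take actual uptake from the timestamps in the intervention arm and from self-report in the control arm; do not assume full uptake. State its assumptions.
3. In the abstract, say that the sample-size increase protects power.
4. Reconcile the two data sections, for example by allowing the statistician early extraction of the contamination items alone.

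The first, third and fourth changes are wording. The second needs some analysis work on data already collected. Its price is precision: at 20% control use the standard deviation of the estimate is about 2.6 points at full uptake and roughly 4.7 to 5.2 at 60% uptake, depending on how uptake is defined, against about 2.1 for ITT. It could therefore be nearly uninformative at 47 per arm if uptake is poor, and it still rests on what controls report.

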#### Missing data

Missing data of multi-item scales will be handled according to questionnaire guidelines. Where guidelines are unavailable, items will be mean-imputed if at least half of the items from the scale are answered. Descriptive statistics are based on complete case analysis. We will analyze available data before imputation for the group comparisons and use the complete case data as a form of sensitivity analysis.

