### Analysis

The CONSORT-EHEALTH recommendations for reporting randomized trials for developing and evaluating eHealth interventions will guide trial reports [48]. Primary and secondary outcomes will be assessed using intention-to-treat analysis where all participants are analyzed according to the arm to which they were randomized. We will conduct a sensitivity analysis separately as described below. The data will be analyzed after all patients have completed the 1-year follow-up. Data will be reported descriptively at each time point. Mean and standard deviation or median and range will be reported for continuous outcomes. Frequency and percentage will be reported for categorical outcomes.

The association between potential covariates and the primary and secondary endpoints will be explored using univariate analysis. Any variables with a *p* value of < 0.1 will be included in the multivariable model. Multivariable analysis controlling for potential covariates associated with the particular outcome will be conducted using logistic regression for binary outcomes and multiple linear regression for continuous outcomes. Two-sided *p* values of < 0.05 will be considered statistically significant.

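### The primary PAM-13 analysis is in effect complete-case under an intention-to-treat label, and no stated sensitivity analysis addresses bias from the expected 23% loss at 3 months

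*Protocol article*

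**What the plan says.** All places are in the protocol article.

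- **Analysis** says that primary and secondary outcomes will be assessed by "intention-to-treat analysis where all participants are analyzed according to the arm to which they were randomized".
- **Primary endpoint** makes the main comparison an independent t test on PAM-13 change, followed by a multiple regression with covariates.
- **Sample size** expects substantial loss by the primary time point: "We will increase the sample size taking 23% attrition at 3 months into account". This takes 47 per group to 61, or 122 in total.
- **Missing data** gives the rule for comparing the arms: "We will analyze available data before imputation for the group comparisons and use the complete case data as a form of sensitivity analysis". The only imputation it describes is mean imputation of items when at least half of a scale has been answered.
- **Sensitivity analysis** plans a per-protocol analysis aimed at contamination.
- **Secondary endpoints** adds a comparison of change in the four validated measures, which include PAM-13, "across the four time points between the intervention and control arm using a mixed models approach".
- **Dissemination** mentions newsletters to participants as a way to limit attrition.

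**The concern.** A change score exists only for someone who returned both questionnaires. The primary test therefore drops everyone without a 3-month PAM-13, while the Analysis section describes a set made up of all participants. The check that should show whether this matters, the complete-case analysis, restores none of the people who were dropped.

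The loss could plausibly be informative. The trial is unblinded and the outcome is self-reported (Study design). Follow-up depends on participants completing online questionnaires (Patient-reported outcome measure data), and the outcome itself is how actively a person manages her care. Under Recruitment, participants learn their allocation before they complete the baseline measure, so even baseline completion could depend on arm. If loss is related to activation and the relation differs by arm, the estimated effect is biased, and the stated check would say nothing about it.

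**Working it through.** **1. Reproduce the plan's figures.** The effect and spread come from Sample size: "this study is planned to detect a mean change difference of 5.90 assuming a common standard deviation of 10.0". The same section sets power at 80% and a two-sided 5% level, and arrives at 47 evaluable per arm.

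- Normal approximation: n = 2 × [10 × (1.960 + 0.842) / 5.90]² = 45.1, so 46 per group. The t-based solution is 46.08, so 47. The stated 47 reproduces.
- Inflation: 47 / (1 − 0.23) = 61.04. The plan uses 61; strict rounding up would give 62, an immaterial difference.
- Total: 2 × 61 = 122.

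**2. Who is in the primary test.**

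- Analysed: 61 × 0.77 = 46.97, about 47 per group.
- Left out: 61 × 0.23 = 14.03, about 14 per group, or 28 of 122.
- Power of the t test with 47 per group is 0.808, so the inflation does its job for precision.

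**3. What the complete-case check can add.** The article defines neither of the two terms. The plausible meanings of complete case, each compared with the set that has both PAM-13 scores, are:

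| Meaning | Relation to the primary set | Restores a missing 3-month questionnaire? |
|---|---|---|
| Both scores present | same | no |
| All items answered | same or smaller | no |
| All covariates present | same or smaller | no |
| All four time points present | same or smaller | no |

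The words about analysing data before imputation might hint at a later imputed analysis. The only imputation described works on items within a partly answered scale, so it cannot supply a questionnaire that was never returned.

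**4. Size of the possible bias.** Let d be how many points less non-completers changed than completers in an arm, and p the share lost in that arm. The completers' mean then overstates the arm's mean by p × d, and

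bias of the arm difference = p(OWise) × d(OWise) − p(control) × d(control).

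The documents give p = 0.23 and nothing about d. The values of d below are assumptions. In this table the gap is in the OWise arm only and control loss is ignorable.

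| Assumed d | Bias = 0.23 × d | Effect in all randomised if completers show 5.90 | Two-sided type I error if there is no true effect |
|---|---|---|---|
| 2 | 0.46 | 5.44 | about 5.6% |
| 5 | 1.15 | 4.75 | about 8.6% |
| 10 | 2.30 | 3.60 | about 20% |

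The type I error uses SE = 10 × √(2/47) = 2.06 and the normal approximation. If the gap were in the control arm only, the bias would have the same size and the opposite sign, against OWise. If p and d were equal in both arms, the bias would be 0.

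**5. Benchmarks.** The article states: "A difference of four points is considered clinically relevant". A completers' effect of 5.90 would correspond to less than 4 points in all randomised once d exceeds (5.90 − 4) / 0.23 = 8.3. The bias would exceed half of the 4 points once d exceeds 2 / 0.23 = 8.7. Both gaps approach one standard deviation of change (10).

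**The case against.** The strongest case on the other side has four parts.

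- **The loss is not ignored.** A reader might infer that nothing in the plan deals with the 23%. The documents do not support that: the sample size is raised for exactly this loss, newsletters aim to reduce it, and the secondary mixed model would normally use partial follow-up under missing-at-random. What remains is narrower. Inflation protects precision only, and the mixed model is not named as a missing-data check on the primary endpoint.
- **The two data sets need not be identical.** A reader might infer that available data and complete cases are one and the same set, so that the check must always agree with the primary result. With both terms undefined, that goes too far. A stricter complete-case set could give a different estimate and show something about item-level gaps, missing covariates or later dropout. It still cannot bring back anyone without a 3-month score, so the point about whole-questionnaire loss stands.
- **The intention-to-treat sentence may be only a rule about allocation,** and the Missing data section openly restricts comparisons to available data. This is fair, and it makes the conflict one of labelling, not concealment. The label still refers to all participants, and the planned test cannot include them.
- **Imputation detail belongs in an analysis plan that is not shown.** That also stands, and the absence of an imputation model is not the point here. The point is that the article does fix a sensitivity analysis for missing data, and the one it fixes cannot answer the question.

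**Conclusion.** The point holds as a limited one. Taken together, Analysis, Primary endpoint and Missing data make the primary result a comparison of about 94 of 122 participants (2 × 47) under an intention-to-treat label. No stated sensitivity analysis of the primary endpoint addresses bias from missing 3-month questionnaires. That part follows from the text and needs no assumption beyond the plan's own 23%.

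The possible size of the bias does rest on assumptions. The figures of 0.5 to 2.3 points need a gap of 2 to 10 points between completers and non-completers in one arm only, and the documents offer no evidence for or against such a gap. A reader might infer that the trial's estimate will be off by a point or two. The documents do not support that: the bias could be negligible, could cancel, or could run against OWise. The present check could not distinguish these cases, and a better one is cheap, so the change is worth making.

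**What to change.** In Missing data, replace the complete-case sensitivity analysis for PAM-13 with two named analyses:

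1. The 3-month arm contrast from the mixed model already planned under Secondary endpoints, adjusted for age group and centre (the stratification factors). Under missing-at-random it brings in participants who miss month 3 but return at 6 or 12 months. Participants with only a baseline score add little.
2. A delta-adjusted multiple imputation, with the shift applied to imputed 3-month values varied separately by arm, to show how large a departure from missing-at-random would change the conclusion. The mixed model alone cannot do this if less engaged participants stop answering altogether.

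In Analysis and Primary endpoint, describe the t test as an available-case analysis by randomised arm, and define available data wherever the term is kept. The mixed model could instead be made the primary analysis, but that is optional: the sample size rests on the t test, and naming the model as a sensitivity analysis is enough to close the gap.

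The cost is revised wording and modest extra analysis. No patients, visits or delay are added, because the analysis already waits for the 1-year follow-up.
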